### Interim analysis {21b}

An exploratory interim analysis of the baseline data collected at t0 is planned when a total of 70 participants have been recruited. The aim is to check whether the baseline data of both study groups are comparable. Access to the analysed interim data will be given to the project leading member (SKF) and the statistician who conducts data analysis (AS).

### Additional analyses {20b}

Subgroup analyses are planned to investigate whether there are differences in primary and secondary outcomes (1) between *BRCA1/2* mutation carriers without a personal history of cancer and those with a personal history of unilateral BC and (2) between women recruited directly after the post-test genetic counselling or later on at an appointment as part of an examination for the intensified breast cancer screening (and aftercare) programme. Subgroup analyses will be performed using the independent *t-*test for normally distributed metric variables, and non-parametric tests will be used in case of non-normal distributions. The chi-square test or Fisher’s exact test will be used for categorical variables. Beyond group allocation, demographic data will be used as the independent variable.

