### Objectives {7}

The aim of this study is to evaluate two newly developed evidence-based DAs for women with pathogenic *BRCA1/2* mutations in Germany with regard to their effectiveness on decision-, psychological- and knowledge-related factors in clinical use and their acceptability with the addressees. We hypothesise that the use of these DAs on top of standard care will reduce the extent of decisional conflict regarding the choice of a preventive option compared to standard care alone (primary outcome). Furthermore, it will be examined whether the use of the DAs can reduce possible symptoms of anxiety, depression or psychological strain associated with the genetic test result, the risk of BC and OC and the available preventive options. Lastly, we hypothesise that at 6-month-follow-up, the intervention group (IG) will feel less regret regarding the choice made compared to the control group (CG).

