### Intervention

Once the completed baseline questionnaires (t0) have been returned to the data evaluation institution, the DAs will be sent by regular mail to those participants randomised to the IG with a request to use the DA for information and decision support at home. Previvors will receive DA-A, and survivors will receive DA-B.

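### The planned subgroup analyses compare outcomes between subgroups and do not test whether the decision aid's effect differs between them

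*Protocol article*

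**What the plan says.** Additional analyses {20b} in the protocol article names two subgroup factors. The first is cancer history: "Subgroup analyses are planned to investigate whether there are differences in primary and secondary outcomes (1) between" carriers without a personal history of cancer and those with previous unilateral breast cancer. The second is recruitment route: "between women recruited directly after the post-test genetic counselling or later on at an appointment" within the screening programme. The method follows: "Subgroup analyses will be performed using the independent *t-*test for normally distributed metric variables", with non-parametric tests otherwise and chi-square or Fisher's exact tests for categorical variables. Allocation appears once: "Beyond group allocation, demographic data will be used as the independent variable". The section names no model with both arm and subgroup, and no interaction.

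Cancer history also decides which product a woman in the intervention group gets. The Intervention section states: "Previvors will receive DA-A, and survivors will receive DA-B". Objectives {7} opens: "The aim of this study is to evaluate two newly developed evidence-based DAs for women with pathogenic" *BRCA1/2* mutations. The primary comparison under Statistical methods {20a} pools both aids, and the Discussion defends evaluating both in one trial.

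**The concern.** A subgroup analysis in a randomised trial should show whether the treatment effect (intervention minus control) varies with a baseline characteristic. The wording of {20b} asks something else: whether outcomes differ between two kinds of women. Previvors and survivors can differ in decisional conflict for reasons unrelated to any brochure. The Background section itself says the decision may be more complex for survivors.

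The sentence on group allocation allows a second reading, in which intervention and control are compared separately within each subgroup. That gives a separate comparison for DA-A and DA-B, which is useful. It is still not a test of whether the effects differ, because one significant and one non-significant p-value can arise from equal effects.

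The cancer-history analysis is the only planned place where the two aid-population pairs are looked at apart. Under the first reading, a prognostic difference could be reported as effect modification. Under the second, unequal subgroup sizes could be.

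**Working it through.** **Inputs from the protocol article.** Sample size {14}: d = 0.3, α = 0.05, one-sided, 139 per group, 10% drop-out, 310 in total. Trial design {8}: 1:1 allocation.

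**Assumptions, because the documents give no figures.** Subgroup split 50:50 to 80:20; prognostic gap 0.3 to 0.4 SD; two-sided 0.05 for contrasts between subgroups. All effects are in SD units of the outcome analysed.

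**1. The plan's own figure.** n = 2(1.645 + 0.842)²/0.3² = 137.4, so 138 by the normal formula. The t-based value is 138.07, rounded up to 139. Then 139/0.9 = 154.4, so 155 per group and 310 in total. This reproduces the plan, with the printed ß of 0.8 read as power.

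**2. What the previvor-versus-survivor t-test measures.** Let g be the gap between survivors and previvors without any aid, and δA and δB the reductions in conflict from DA-A and DA-B. With 1:1 allocation, half of each subgroup receives an aid, so the expected difference between subgroups is

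g + (δA − δB)/2.

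The test mixes prognosis with half the difference in effect. At 50:50 each subgroup has 139 women. With equal effects of 0.3, the SD within a subgroup is √(1 + 0.15²) = 1.011, and the SE is 1.011 × √(2/139) = 0.121.

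- g = 0.3: Φ(0.3/0.121 − 1.96) ≈ 70%; simulation of 5,000 trials gives 69%.
- g = 0.4: Φ(0.4/0.121 − 1.96) ≈ 91%.

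Simulated share of significant results, 139 per arm, 50:50:

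| Scenario | Expected subgroup difference | Subgroup t-test | Interaction test |
|---|---|---|---|
| g = 0.3, δA = δB = 0.3 | 0.3 | 69% | 5% |
| g = 0, δA = 0.6, δB = 0 | 0.3 | 69% | 71% |
| g = 0.3, δA = 0, δB = 0.6 | 0 | 5% | 69% |

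The t-test cannot tell the first two rows apart, and it misses the third.

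**3. The within-subgroup reading.** Power for d = 0.3, one-sided 0.05, with m per arm in the subgroup is Φ(0.3/√(2/m) − 1.645).

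- 50:50, m = 69.5: 55% in each subgroup.
- 80:20, m = 111.2 and 27.8: 72% and 30%.

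With equal true effects, the chance that exactly one subgroup is significant is 2 × 0.55 × 0.45 ≈ 50% at 50:50, and 0.72 × 0.70 + 0.28 × 0.30 ≈ 59% at 80:20.

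**4. What a proper interaction test can do.** Without baseline adjustment, SE = √(2/a + 2/b), where a and b are the subgroup sizes per arm and a + b = 139. The difference detectable with 80% power is (1.960 + 0.842) × SE.

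| Split | SE | Power for 0.3 SD difference in effect | Detectable at 80% |
|---|---|---|---|
| 50:50 | 0.240 | 24% | 0.67 SD |
| 70:30 | 0.262 | 21% | 0.73 SD |
| 80:20 | 0.300 | 17% | 0.84 SD |

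Baseline adjustment would help. With an assumed baseline correlation of 0.5, SEs shrink by √(1 − 0.25) = 0.866, giving 0.208 and a detectable difference of 0.58 SD at 50:50.

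**The case against.** The strongest reply is that {20b} is ambiguous rather than wrong. It names allocation as an independent variable, so it may intend intervention-versus-control tests in each stratum. These would show whether each aid works against standard care, which is what Objectives {7} asks; no objective asks whether the two effects differ. This stands in part. A reader might infer that the plan cannot evaluate the two aids separately at all, and the documents do not support that. But the section's opening sentence describes comparisons between subgroups, and neither reading tests a difference in effect. This is a matter of the method stated, not of detail left to a fuller document.

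Second, the abstract and Outcomes {12} define the primary outcome as change in decisional conflict, and a stable baseline gap cancels in a change score. That is correct. With change scores, the false signal needs a gap in how conflict evolves without an aid. Statistical methods {20a} words the outcome more loosely, as decisional conflict at t1; if raw t1 scores are compared, a baseline gap is enough.

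Third, aid and cancer history are completely confounded, so even an interaction test cannot compare the two brochures as products. This stands, and the report must say so.

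Fourth, these are additional analyses, and the replacement test has little power. Both are true. They limit the seriousness of the point but do not justify a test of a different question.

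**Conclusion.** The point holds as a defect in the stated method of an exploratory analysis. On its plain reading, {20b} contrasts prognosis; on the alternative reading it gives two separate comparisons and no test of their difference. The 69% to 91% rate of misleading significance is an illustration. It rests on an assumed gap of 0.3 to 0.4 SD in the analysed outcome, an assumed even split, 139 evaluable women per arm and two-sided 0.05.

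Two stronger conclusions might be inferred, and neither is supported. The main result is not compromised: the pooled primary test, 139 per group and 310 in total do not depend on this section. Nor does the protocol tie adoption of either aid to a subgroup result; the Discussion says both will be integrated into care after the evaluation. The risk is one of misinterpretation, so the wording should be corrected, but this is not a critical flaw.

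**What to change.** Restate {20b} so that each subgroup analysis fits a linear model for the DCS with arm, subgroup, arm-by-subgroup interaction and baseline DCS. Treat other continuous outcomes the same way, dropping the baseline term for scales with no baseline measurement, such as decision regret. Use logistic or ordinal models with the same interaction for categorical outcomes.

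For each factor, report the intervention-minus-control difference with 95% CI in each subgroup, and the interaction estimate with its CI. For cancer history, label the two differences as DA-A in previvors and DA-B in survivors. State that:

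- the analyses are exploratory;
- the cancer-history interaction compares aid-population pairs, because aid and history cannot be separated;
- a non-significant interaction does not show equal effects;
- power is low, with the figures above given for the split actually observed.

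The cost is a change of analysis wording and a model that {20a} does not currently contain; the primary t-test need not change. No new data are needed, so the change remains possible although recruitment has closed. It should be dated before the analyst learns the group codes.

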### Definition of analysis population {20c}

All analyses will be conducted following the intention-to-treat (ITT) principle including all randomised patients. No imputation of missing values will be performed.

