### Enrolment and randomisation

Recruitment takes place during a specialist consultation either (1) directly following the post-test genetic counselling or (2) during a medical examination as part of the intensified breast cancer screening programme (for previvors, A) or the intensified breast cancer screening and aftercare programme (for survivors, B). If the inclusion criteria are met, eligible women will be informed about the study and invited to participate. Women who agree to do so will be asked to provide informed consent. Physicians will complete a recruitment form. Thereafter, participants are randomly assigned to one of the two study groups. The allocation is blinded to both the recruiting physicians and the participants.

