### Outcome data collections at t1 and t2

Participants, who have returned the baseline questionnaire (t0), will receive the follow-up questionnaire at t1 at 3-month-follow-up with the request to return the completed questionnaire within two weeks by regular mail. Participants who have returned the questionnaire t1 will receive the next follow-up questionnaire at t2 at 6-month follow-up with the request to return the completed questionnaire within two weeks by regular mail.

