#### Promoting participant retention and complete follow-up {18b}

Participants who did not return the questionnaires in time will receive up to two postal reminders with the request to send the questionnaires back within 1 week. Those who still will not react will be contacted again by telephone to encourage participant retention. This will be done by the study nurse who works with the recruiting team.

Women assigned to the CG do not receive DAs and may, therefore, be more likely to drop out of the study than women assigned to the IG. To counter this possibility of higher drop-out rates, all women in the CG are offered to request a DA when the last follow-up questionnaire at t2 is returned. This is to ensure that they can participate in the study without being disadvantaged.

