The procedures in the study have some limitations which, however, cannot be avoided due to the nature of this type of intervention chosen. One limitation is that there is no guarantee that all IG participants will actually use the DAs which they will receive per regular mail and are invited to use at home. In order to comply with the voluntary nature of the study participation and to avoid exerting any pressure on study participants, the follow-up questionnaire at t1 which collects data after receipt of the DA does not ask whether the DA was actually used. Therefore, the research team will receive no feedback as to whether and if so, to what extent the women have worked with the DA. On the other hand, discussions with the members of the BRCA network and with medical specialists who provide genetic counselling indicated that many women with *BRCA1/2* mutations hope for a device in which all aspects of their decision-making process are explained and brought together. A further limitation refers to the possibility that study participants might get in contact with each other. For example, due to the hereditary nature of the gene mutation, multiple family members may take part in the study. In this case, women assigned to the CG or women at baseline could unintentionally have access to the DA. It will also remain unclear, to what extent the study participants will use other sources of information or support. Such interferences may contaminate the collected data to a certain extent. Yet, there is no way to prevent this and accessing additional information is assumed to happen equally in the IG and CG. Another limitation refers to the blinding of participants, which is not possible throughout the entire course of the present trial. Since all participants will be informed in detail about the course of the study before inclusion into the study, they all are aware that they may or may not receive the intervention. Blinding of the participants can therefore only be guaranteed at baseline (t0). For IG participants, unblinding occurs at the moment they receive the DAs. CG participants are unblinded at the latest when they receive the follow-up questionnaire at t1 and have not yet received the DAs. It seems most appropriate to examine the impact of both DAs in a setting that reflects the current concept of standard care. This implies that the CG participants do not receive other information than that provided by the current concept. Finally, it cannot be excluded that there may be a bias due to non-response by not returning questionnaires, especially if non-response rates should differ between IG and CG.

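### The analysis is labelled intention-to-treat on all randomised women, but the mailing rule, the tests and the no-imputation rule make it a complete-case analysis

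*Protocol article*

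**What the plan says.** The section Definition of analysis population {20c} makes two statements, one after the other: "All analyses will be conducted following the intention-to-treat (ITT) principle including all randomised patients. No imputation of missing values will be performed".

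Other sections determine who can have a primary outcome:

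- **Randomisation comes first.** After consent and the recruitment form: "Thereafter, participants are randomly assigned to one of the two study groups" (Enrolment and randomisation). The baseline questionnaire is filled in at home afterwards.
- **Follow-up is conditional.** "Participants, who have returned the baseline questionnaire (t0), will receive the follow-up questionnaire at t1", and then "Participants who have returned the questionnaire t1 will receive the next follow-up questionnaire at t2" (Outcome data collections at t1 and t2).
- **The primary outcome is a change.** Outcomes {12} defines it as the change in DCS, assessed at t1. Section {20a} compares the groups with an independent t-test, or a non-parametric test if the data are not normal.

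The protocol also discusses non-response. Section {18b} says that control women "may, therefore, be more likely to drop out of the study than women assigned to the IG". It provides up to two postal reminders, a telephone call, and a decision aid on request for control women after t2. The Discussion concedes that "there may be a bias due to non-response by not returning questionnaires, especially if non-response rates should differ between IG and CG".

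**The concern.** An intention-to-treat claim on all randomised women tells the reader that the comparison keeps the full protection of randomisation. Here it does not, because a woman with no t0 or no t1 questionnaire drops out of the primary comparison. The two kinds of loss differ in what they do:

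- **Loss before t0.** Participants are still blinded (Blinding {17a}) and no decision aid has been sent. This loss contradicts the all-randomised claim but should not depend on arm.
- **Loss at t1.** Intervention women know their arm once the decision aid arrives, and control women at the latest when the t1 form arrives without one (Unblinding {17b}). This loss can depend on arm. The outcome is self-reported, so it can shift the primary difference.

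At stake is a primary result presented as intention-to-treat while it carries a bias that the protocol itself names.

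**Working it through.** **1. Can the stated set be analysed?**

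| Step | Rule | Consequence |
|---|---|---|
| Randomised | After consent, before t0 return | Enters the all-randomised set |
| No t0 | No t1 form is sent | No t1 score, and none is imputed |
| t0 but no t1 | No t2 form is sent | No change score |
| t0 and t1 | Change score exists | Analysed |

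Only the last row reaches the test. Section {20a} can also be read as testing the t1 score itself. The same women are then analysed, because nobody has t1 without t0.

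**2. The protocol's own sample size.** Inputs from Sample size {14}: d = 0.3, one-sided α = 0.05, power 0.80, drop-out 10%. Power comes from the noncentral t distribution with noncentrality d / √(1/n₁ + 1/n₂).

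- n = 139 per group: 0.3 / √(2/139) = 2.501, power 80.2%. The stated 139 is reproduced.
- 139 / 0.90 = 154.4, rounded up to 155 per group, 310 in total. Reproduced.
- Back-check: 155 × 0.90 = 139.5 per group.

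The trial is therefore sized on women who remain after drop-out, not on all 310.

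**3. Size of the bias from t1 loss.** The protocol gives no loss rate by arm and no difference between non-responders and responders. The figures below are assumptions. If non-responders differ from responders by g (in SD of the analysed outcome, the same in both arms), the completer mean in an arm is off by loss × g, so

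bias = (control loss − intervention loss) × g.

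- 15% vs 5%, g = 0.25: 0.10 × 0.25 = 0.025 SD (8% of 0.3).
- 15% vs 5%, g = 0.5: 0.10 × 0.5 = 0.05 SD (0.05 / 0.3 = 17%).
- Equal losses and equal g: 0.

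**4. Consequence at 15% vs 5%, g = 0.5.** Completers: 155 × 0.95 ≈ 147 and 155 × 0.85 ≈ 132.

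- No bias: power at d = 0.3 is 80.3%, so uneven loss alone costs little.
- Non-responders have more conflict: control completers look better, and the apparent effect is 0.30 − 0.05 = 0.25. Noncentrality 2.085, power about 67%.
- Non-responders have less conflict and there is no true effect: the apparent effect is 0.05. Noncentrality 0.417, one-sided error about 0.11.

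**5. What baseline adjustment can do.** Let ρ be the correlation of t0 and t1 DCS (assumed 0.5), with equal SD at both times, the same losses, and g = 0.5 on the score that drives the loss. Sizes of bias in SD:

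| Loss depends on | Change score | Baseline-adjusted (ANCOVA) |
|---|---|---|
| t1 DCS | 0.05 × (1 − ρ) = 0.025 | 0.05 × (1 − ρ²) = 0.0375 |
| t0 DCS | 0.05 × (1 − ρ) = 0.025 | 0 |

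Simulation agrees: about 0.023 to 0.025 and 0.036 to 0.038 in the first row, and about 0.024 and 0 in the second. Adjustment removes the bias when loss depends on baseline, but not when it depends on the t1 score.

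**The case against.** The strongest reply is that this is only a label. The no-imputation rule is disclosed directly after the claim, the sample size is built on women who remain, section {18b} takes practical steps to limit drop-out, and the Discussion admits possible non-response bias. Methods for missing data are commonly left to an analysis plan, which is not shown here.

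Much of this stands. Declining to impute is not an error, and the absence of a sensitivity analysis from an article is not counted against it. The contradiction remains, because the protocol itself fixes the set, the tests and the no-imputation rule. An analysis plan could not produce the promised set without overriding one of them.

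A reader might infer more than the document supports:

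- *That higher control drop-out is expected.* Section {18b} treats it as a possibility, and the sample size uses one rate for both arms.
- *That the trial is underpowered because loss builds up over two questionnaires.* The protocol gives a single 10% and no rate per step, and that figure leaves 139 per group and 80% power.
- *That the bias must favour the decision aid.* If more control women are lost and they have more conflict, it works against the decision aid.
- *That a completer change-score test is the worst choice and a mixed model would cure it.* Neither method is less biased in every case (working, step 5). Because t2 is sent only after t1, t2 data add almost nothing to the t1 comparison.

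**Conclusion.** The point holds. As written, the all-randomised claim cannot be met, and the primary analysis is a complete-case analysis of women with t0 and t1. Loss before t0 damages the label only. Loss at t1 can bias the primary difference in either direction: about 0.05 SD under losses of 15% and 5% with a 0.5 SD gap, with power about 67% or one-sided error about 0.11 depending on direction. These rates and gaps are assumptions, and with equal losses and equal gaps the bias is zero. The document does not show that material bias will occur. It shows that a bias it foresees would be reported under a label implying its absence.

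**What to change.** Replace the sentence on the analysis population with, for example:

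> The analysis set is all randomised women who returned t0, analysed as randomised. The primary comparison uses those with a t1 DCS score. Non-return at t0 and at t1 is reported by arm.

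Then make two changes to the analysis:

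1. Estimate the t1 difference with adjustment for baseline DCS, by ANCOVA or an equivalent likelihood model that keeps women with t0 only. This deals with loss that depends on baseline DCS.
2. Add an arm-specific delta (tipping-point) sensitivity analysis for t1 non-response. This is the part that addresses loss depending on the t1 score, which adjustment cannot repair.

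Cost: the all-randomised claim is given up, and a little analysis work is added in SPSS or R, both already named. No new data are needed, so the change remains possible although recruitment has closed. It is best made before the group codes are opened.
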